#### Power

We will conduct the primary analysis evaluating mean differences of change in study outcomes by PE group assignment. With a sample of 50 (PE pairwise comparisons between the 2 intervention groups and controls) assuming an alpha of.05 and improvements of controls at a rate similar to 12-month change previously seen, we have 94% power to assess a 50% greater improvement in systolic blood pressure in the intervention group, and 79% power to assess a 40% greater improvement. We will have >99% power to detect differences in efficacy analyses. We believe that these are realistic goals based on results of other rigorous mHealth studies in LMIC [24]. Power calculations were completed using STATA (StataCorp College Station).

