**Methods:**

The study design is a cluster randomized controlled clinical trial randomizing each of 75 Community peer educators (PEs), trained and coordinated by MoPoTsyo Patient Information Center in Phnom Penh, into one of 3 groups of 25 (approximately 60 patients each) to receive either tablet+messages, tablet only, or no intervention (control). The total sample within each group includes 25 clusters and approximately 1500 patients located in 7 Operational Districts in rural regions or urban slums in Cambodia. The interventions (groups 1 and 2) were compared with usual PE monitoring without the tablet or mHealth messaging interventions. Focus groups and informant interviews were conducted to develop messages according to specific themes—medications adherence, laboratory testing, physician visits, obesity, smoking, and general lifestyle issues. Using the data received at monthly PE monitoring meetings, patients will receive specific messages based on their individual health challenges. Following the intervention completion, clinical and process outcomes will be compared with baseline metrics between groups.

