**Conclusions:**

This project is unique in its combination of electronic data transfer, which can be accessed immediately, with voice messages most relevant to individual patients’ needs. Positive results will indicate the value of using targeted messaging in patient-specific, self-management issues to improve hypertension and diabetes control.

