## Methods

### Human Subjects Approval

This is a randomized controlled clinical trial to test an intervention comprising faster data capture plus targeted voice messages compared with PE monthly monitoring in a community-based sample in Cambodia for improvement of hypertension and diabetes outcomes. This study received Institutional Review Board approval from the University of Washington Division of Human Subjects and the National Ethics Committee for Health Research in Cambodia. All PEs, regardless of study allocation, and participants assigned to the telephone message intervention provided written informed consent. Informed consent from community participants who did not receive mHealth messages were waived by the Institutional Review Boards as routine monitoring provided study outcome data for these groups. This study was determined to not qualify as an “Applicable Clinical Trial” according to the National Institutes of Health definition [16] at the time it was initiated and, thus, was not registered in clinicaltrials.gov. As the risk of harm is minimal in this study, no criteria for discontinuation were developed. An Advisory Committee comprising Cambodian Ministry of Health officials, health care providers, and technology experts was convened to provide oversight and guidance to the study.

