### Approach

In this study, we are collaborating with MoPoTsyo Patient Information Center to enhance their Peer Educator Network model through the application of mHealth-tailored phone messaging and improved eHealth communication throughout the system. A focus on hypertension, justified by the extremely low medication adherence of hypertensive patients compared with diabetic patients, shifts the intervention to an area of great need. Two interventions will be tested, one at the PE level and one at the patient level. The first includes providing electronic tablets to PEs for data collection and transfer to the MoPoTsyo database in Phnom Penh. The tablets are intended to speed up data collection and entry, reduce paper, increase accuracy, and eliminate lengthy distances that must be traveled to bring paperwork to MoPoTsyo. In addition, the tablets will allow PEs to scan a patient’s record “handbook” (log kept with the patient) to be verified by MoPoTsyo quality control staff should data appear suspicious. At the patient level, voice messages developed to address specific patient problems (eg, uncontrolled blood pressure or glucose, medications not picked up at the pharmacy, weight gain, etc) will be sent to patients based on the data received from the monthly visits to the PE. This study has randomly selected 75 PEs for assignment to 1 of 3 intervention groups—tablet+messaging, tablet only, or control (no tablet or voice messages). Figure 1 shows the study design. As we estimate that each of the 25 PEs in each group monitors about 60 patients, each arm of the study will include about 1500 participants for a total community sample of about 4500.

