### Electronic Data Capture

Fifty PEs (25 in the tablet+messaging group and 25 in the tablet only group) received a 12-inch Chuwi Hi12 Tablet with touchscreen compatible for Windows 10-Android 5.1 to record patient information each month. Data are entered online or offline during the patient visit with backup recorded in the patient handbook (log). Data are transferred to the MoPoTsyo database stored on a Dell PowerEdge T630 Server, RAM 32GB (Gigabytes), HDD 4TB, (hard disk 4 Terabytes), speed 2.4 GHz, Cache 20MB. The operating system is Windows Server 2012R2 with database application Microsoft SQL server 2014. Initial training has been provided by MoPoTsyo staff to assure PEs are comfortable with using the tablets for their monthly monitoring visits. It has become clear, perhaps because of their older age and lack of experience, that many of the PEs are challenged by the technical aspects of this new tool. We have begun weekly Web-conferences (broadcast on the tablets) to help address problems and increase PE skills in tablet use. In addition, pharmacies have received tablets to input prescriptions and provide information to MoPoTsyo regarding invoices when medications are purchased. We do not anticipate significant dropout of PEs based on historical experience. PEs seldom leave MoPoTsyo unless illness or death intervenes. Retention efforts for community participants include the free health monitoring provided by PEs and the social interactions that result in this popular program. PEs in all groups are coached to be vigilant in responding to patient questions and needs as well as to contact the MoPoTsyo Center with any issues that arise.

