#### Statistical Analyses

Statistical analysis will be performed collaboratively between Cambodian collaborators and the University of Washington to provide experience to them in this activity. All outcomes, both process and clinical, will be described as N (%) or mean (SD) for categorical and continuous data, respectively. Changes in primary study outcomes, including blood pressure, fasting glucose, and medication adherence, will be calculated as the difference from the baseline to 12-month follow-up. We will evaluate study results 3 ways—first as an intention-to-treat comparison of study outcomes associated with patients in the intervention group versus the control group compared by a change in PE overall clinical outcomes for their patients (mean blood pressure, fasting glucose, and medication adherence). In addition, we will conduct an efficiency analysis using linear regression for the study outcomes evaluating group assignment, as well as other variables, calculated at the PE level (ie, % women, mean education, etc). Finally, we will analyze data at the patient level using Generalize Estimating Equations for each outcome evaluating group assignment and clustering data on PE. Primary dependent variables will include changes in the 3 pre and post continuous clinical outcomes—systolic and diastolic blood pressure, fasting blood glucose, and medication adherence as an intermediate outcome. Covariates will include demographics, baseline clinical values, and urban or rural residency of patients. In these analyses, we will use complier-average causal effects (CACE) to look at the efficacy and effectiveness of the mHealth intervention, which takes the clustering effect of PEs, as well as response of patients into consideration. In these patient-level models, we will conduct an intention-to-treat analysis to evaluate the total causal effect of assigning a PE to the mHealth intervention, regardless of compliance. CACE will also allow us to estimate the mHealth intervention’s effectiveness on patient compliers, considering phone messages received and listened to. In CACE, actual treatment received (compliance to the mHealth treatment) becomes a postrandomized variable and effectiveness based on process outcomes (reach and compliance) are addressed. Analyses will be performed using STATA (StataCorp College Station). No interim analyses are planned.

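### The randomised contrast that separates the voice messages from the tablets is neither named nor powered, yet a positive result is to be credited to messaging

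*Protocol article*

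**What the plan says.** The Approach section sets out three arms: "tablet+messaging, tablet only, or control (no tablet or voice messages", with 25 PEs in each. It presents the tablet and the messages as two interventions, one acting on the PE and one on the patient.

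Four places name a comparator, and in each it is the control:

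- Abstract, Methods: "The interventions (groups 1 and 2) were compared with usual PE monitoring without the tablet or mHealth messaging interventions".
- Human Subjects Approval, where the trial is described as testing "faster data capture plus targeted voice messages compared with PE monthly monitoring".
- Statistical Analyses, first of the three evaluations: a PE-level intention-to-treat comparison of the intervention group with the control group.
- Power: 50 PEs per comparison, described as "PE pairwise comparisons between the 2 intervention groups and controls". The effect to be detected is likewise expressed relative to how much the control arm is expected to improve.

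The other analyses in Statistical Analyses leave the comparator open. The PE-level regression and the patient-level GEE evaluate group assignment without a reference group. The CACE text speaks of assigning a PE to the mHealth intervention and estimates "effectiveness on patient compliers, considering phone messages received and listened to", again without saying against which arm.

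The Abstract's Conclusions then state: "Positive results will indicate the value of using targeted messaging in patient-specific, self-management issues".

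**The concern.** The tablet-only arm exists so that the messages can be separated from the tablet. A comparison of tablet plus messages with control cannot do that, because the two arms differ in both components.

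The protocol does not treat the tablet as inert. The Approach section expects it to speed up data handling and improve accuracy, and it lets headquarters check suspicious entries against a scan of the patient's handbook. Electronic Data Capture adds support for PEs who have tablets: "We have begun weekly Web-conferences (broadcast on the tablets"). According to Human Subjects Approval, routine PE monitoring supplies the outcome data for the arms without messages. The way blood pressure and glucose are recorded therefore differs between tablet and control arms.

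If the conclusion is drawn from the contrasts that are named, any effect of the tablet, its support or its recording mode is credited to the messages. The results are meant to inform Ministry of Health recommendations, and tablets and messages can be adopted separately.

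**Working it through.** **1. Contrasts against the conclusion**

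| Place | Contrast | Separates messages from tablet? |
|---|---|---|
| Abstract, Methods | groups 1 and 2 v control | No |
| Human Subjects Approval | data capture plus messages v PE monitoring | No |
| Statistical Analyses, PE-level ITT | intervention v control | No |
| Power | each intervention group v control, 25 v 25 | No |
| PE-level regression; GEE | group assignment, reference not stated | Only if all three arms are entered and this contrast is extracted |
| CACE | assignment to mHealth, comparator not stated | Only if tablet only is the comparator |
| Outcomes, comparison across message topics | not described as a comparison of randomised arms | No |
| Abstract, Conclusions | a positive result shows the value of targeted messaging | Requires tablet plus messages v tablet only |

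**2. The stated power**

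Inputs from the Power section: 25 v 25 PEs, alpha 0.05, 94% power for a 50% greater improvement in systolic pressure, 79% for 40%. The control change and the between-PE SD are not given, so the absolute power cannot be reproduced. The two figures can be checked against each other.

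- Normal approximation, two-sided: power = Φ(d·√(n/2) − 1.96), with n = 25 and √12.5 = 3.536.
- 94% requires d·3.536 − 1.96 = 1.555, so d = 3.515/3.536 = 0.994. A noncentral t calculation gives 1.015.
- A 40% effect is 0.8 of a 50% effect: 0.8 × 3.515 − 1.96 = 0.852, and Φ(0.852) = 80.3%. The protocol says 79%. If 94% is a rounded 93.5%, the prediction is 79.4%, so the two figures agree.
- A one-sided test would predict 82.0%, which fits less well. The sidedness is not stated; two-sided is used here.

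**3. Power for the message contrast**

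Assumptions: tablet plus messages gains 50% over control in total, the effects add, and the implied SD applies. The share due to the tablet is not in the protocol, so a range is shown. With tablet share s, the standardised difference is 0.994 × (1 − s).

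| Share of the gain due to the tablet | d | Power, 25 v 25 | PEs per arm for 80% |
|---|---|---|---|
| 0 | 0.994 | 94% | 16 |
| one fifth | 0.795 | 80% | 25 |
| two fifths | 0.596 | 56% | 45 |
| half | 0.497 | 42% | 64 |

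**4. CACE, if control were the comparator**

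Let c be the proportion of patients who receive and listen to messages, m the message effect in those patients, and t a tablet effect on every patient of a tablet-equipped PE. The intention-to-treat difference from control is c·m + t. Dividing by c gives m + t/c. The exclusion restriction needs t = 0, but patients who hear no message still have a PE with a tablet. Against tablet only, t cancels. The protocol gives neither t nor c, so the size of t/c cannot be derived.

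**The case against.** A reader might infer that every planned contrast, CACE included, is against control, and that the exclusion restriction is therefore violated. The protocol does not support that. The regression, GEE and CACE name no reference arm, and a three-level group term could yield tablet plus messages versus tablet only. The doubt about CACE is conditional on control being its comparator and on the tablet affecting patients. Any bias quoted in mmHg would rest wholly on an assumed tablet effect and an assumed compliance rate.

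It can also be said that the package is a legitimate target. The Introduction aims at data capture combined with messages, the Abstract's Conclusions mention that combination just before the sentence on messaging, and the messages are triggered by electronically sent data. The web-conferences and the recording mode belong to the tablet component, so there are two components, not several. A power statement does not list all analyses, and a condensed article may leave a CACE reference arm to the analysis plan.

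Much of this stands. It does not remove the mismatch, because a comparison aimed at the package supports a claim about the package, while the closing sentence of the Conclusions claims more. That is a conflict between what the article states as its contrasts and what it states as its inference, not a missing detail.

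**Conclusion.** The point holds in a limited form. All contrasts with a named comparator, and the power calculation, are against the no-tablet control. Tablet plus messages versus tablet only is neither specified nor powered, although its arms are randomised, and the Abstract's Conclusions attribute a positive result to messaging. Followed as written, the plan could credit a tablet or recording effect to the messages.

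The stated 94% applies to the messages only if the tablet has no effect. Under the assumptions above it is about 80%, 56% or 42% if the tablet supplies one fifth, two fifths or half of a 50% gain. For CACE, the defect is an unstated comparator, with a doubtful exclusion restriction if control is used.

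**What to change.** - Specify the intention-to-treat contrast of tablet plus messages versus tablet only (25 v 25 PEs) as the test of the messages, alongside the two contrasts with control, and give it a place in the testing order.
- Name tablet only as the CACE comparator.
- In both arms, analyse all patients registered when the PEs were randomised, whether or not they agreed to messages. Written consent and the collection of phone numbers applied only to message-arm patients, so restricting that arm to consenters would introduce selection after randomisation. The two tablet arms still differ in this consent contact as well as in the messages, which should be acknowledged.
- Limit the conclusion on messaging to this contrast, and describe tablet plus messages versus control as the effect of the package.
- The article reports data cleaning and analysis as under way, so date the specification and say whether outcomes by arm had already been seen.

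The cost is wording and one more contrast in the testing order, because the arm and its data already exist. Power will be below the stated 94% unless the tablet does nothing, so a null result on the messages should be reported with its confidence interval and not read as absence of effect.

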## Results

Results of the qualitative research were used to develop the telephone messages according to 6 themes—medications adherence, laboratory testing, physician visits (either annual or for alert determined at PE visit), obesity and weight gain, smoking, and general lifestyle issues (diet, exercise, salt intake, etc). Based on the identified facilitators and barriers, the messages are designed to provide education, motivation, and reminders to help support self-management and address obstacles. Specific scripts were tested with patients and recorded in Khmer by a professional recording studio (Women’s Media Center of Cambodia) using music and voice intonations suggested by advisors.

An algorithm was developed to identify patients needing specific content messages based on the most recent data that were sent electronically to the MoPoTsyo database by the PEs. The delivery of messages was decided according to focus group suggestions, including the use of voicemails rather than text, sending messages at dinnertime or shortly afterward so that a person is at home and can share with family members, limiting frequency to 2-3 messages per week, and eliminating interactive requirements owing to limited access to smartphones and lower cell phone literacy in many rural communities. Results of Verboice tracking allows us to determine which messages successfully reached patients (for later efficacy analyses) and allows the system to send messages additional times when not initially completed.

The focus groups and informant interviews used to develop the mHealth messages were completed during the Spring of 2017. Results of this qualitative work were used to develop the mHealth messages, which were then tested over the summer. Following several revisions of content wording, music, and messenger voice, messages were finalized in July 2017 after which InSTEDD provided channels for delivery of specific themes of message to patients identified by PE data. While the implementation was originally scheduled for 6 months from September 2017 to March 2018, the period was extended 4 additional months because of budgetary efficiencies. Data are currently being cleaned and analyzed. We project that we will have results by Spring 2019.

We plan to disseminate results of this study through workshops and presentations to our Advisory Committee, the Cambodian Ministry of Health (Department of Preventive Medicine), and other health partners (eg, National Institute of Public Health in Phnom Penh) and technology experts (private and public). Furthermore, results will be available in report and presentation format on the website of MoPoTsyo Patient Information Center and the University of Washington Department of Family Medicine. We will use the results of the study to provide evidence-based recommendations to the Ministry of Health as they prepare pilot and other programs and policy for addressing NCDs across Cambodia.

## Discussion

This protocol provides information on a new intervention to develop and test mHealth and eHealth interventions to utilize an existing peer support network for improving hypertension and diabetes management in Cambodia. Our formative work, to develop and pilot-test the messages and distribute the tablets, suggests that his approach may be feasible in other LMIC.

The value of peer support in chronic disease management has been well documented and is a viable alternative when health care infrastructure is inadequate to meet needs [25]. While mHealth messaging programs have rapidly increased in LMIC, evaluations of these programs remain limited and provide inconsistent results [26]. The variety of different features and measured outcomes included in such studies also makes comparisons difficult. While the majority of studies in the literature utilize SMS text messaging, we chose voice messages in our intervention owing to the low literacy rate of our target population. In addition, other mHealth studies in low-resource settings have documented a preference for voice messages by targeted populations. For example, 99% of mothers participating in the Mobile Midwife program in Ghana preferred voice messages over text [27]. Similarly, a study of 488 mobile phone users in India found that 89% preferred to receive medication reminders by voice calls over SMS text messages [28]. Several other studies selecting a voice approach have reported positive results [29-31].

Interactive systems, allowing the recipient to respond to a message on their phone pad, have suggested benefits, although we chose to exclude such a feature as our focus groups informed us that this was confusing to patients. In terms of outcomes, many studies have reported benefits in proxy measures, such as medication adherence, clinic attendance, or behavioral change [30,32-36]. Although improvements in clinical outcomes may be of greatest value in disease control, studies reporting these outcomes are unfortunately less common [13,29,37,38]. Finally, while it is established that mHealth messaging systems involving personalized content are generally more successful [39], personalized interventions are also less common in LMIC, and accessing patient data that are both appropriate and timely may not be possible in many of these settings. As mHealth solutions for electronic health recording and data capture increase, tools for monitoring and accessing timely patient data can provide community health workers, PEs, and providers the information they need to offer relevant and personalized care to patients. Such an approach may be especially useful for managing patients with chronic conditions. This protocol was designed to address these barriers.

While this protocol has many strengths, including the stable infrastructure and PE training already in place by MoPoTsyo, there are a number of limitations, which primarily involve the ability of the targeted messages to reach participants. Problems may involve cell phone network coverage and reliability, cell phone number changes, use of phones across family members, and lack of interest in listening to the messages. Other problems may include the reluctance of PEs to use the tablets in a timely manner, loss of tablets, and factors outside of our control (ie, lack of money to cover medications, etc). While strategies have been developed to minimize these issues, they may still impact the effect of the intervention.

The protocol described here represents an effort to integrate improved data technology for collecting data (eHealth) with individualized voice messaging (mHealth) to encourage self-management of hypertension and diabetes in a low-resource setting. We hypothesize that targeting specific health issues of relevance to patients will be more effective in encouraging good behavior than generic messaging often used in mHealth studies. We hope to show that the promotion of greater communication across providers and patients is feasible in LMIC and will result in better clinical outcomes for their patients.

